##### Analysis

The acquired admission CT data are stored on an online secured server in the University Medical Center Utrecht. Standard post-processing of the data with 5-mm CTP reconstructions will be performed with Intellispace software (Philips Healthcare, Best, The Netherlands). In addition, the thin-slice CTP source data will also be reconstructed with iterative reconstruction and processed with in-house developed CTP software to enable detection of small volume strokes on admission CTP.^27^ If the subject is scanned on the Philips IQon Spectral CT, the dual-energy CTP dataset will be used to reconstruct images including virtual monoenergetic images, virtual non-contrast images, and iodine maps. The obtained perfusion maps will be evaluated for the presence and location of a focal perfusion deficit matching a part of a cerebral artery flow-territory. Fat and calcium volume of internal carotid artery atherosclerotic plaque will be determined on dual-energy CTA. The admission non-gated cardiac CTA will be evaluated for the presence of thrombus, left atrial size and atrial appendage morphology, patent foramen ovale or other septal defects, signs of previous myocardial ischemia or non-ischemic cardiomyopathy, aneurysm, valvular abnormalities, and signs of endocarditis. Imaging assessments will be done by experienced observers, who will be blinded to clinical data.

### Follow-up data

#### Cardiac imaging

In case follow-up imaging of the heart (e.g. transthoracic or transesophageal echocardiography, CT, or MRI) is performed, the same variables will be evaluated as for baseline cardiac CTA. Other remarkable findings will be noted. Findings from continuous ECG monitoring or Holter ECG will also be recorded.

#### MR imaging

Patients who fulfill the selection criteria for the MRI-part of this study will undergo MRI of the brain and neck within 48 h after presentation. MRI findings will serve as the gold standard for the detection of cerebral ischemia. The MRI protocol will include diffusion-weighted imaging (DWI) and 3D fluid attenuated inversion recovery (FLAIR) sequences of the brain, and, if feasible, MR angiography (MRA) of the neck, vessel wall imaging of the intracranial arteries, and simultaneous non-contrast angiography and intraplaque hemorrhage (SNAP) sequences of the extracranial carotid arteries.^28^ Participants will be scanned on 3T MRI scanners from different vendors. If 3T MRI is not available for logistic reasons, FLAIR and DWI sequences can be acquired on 1.5-T MRI scanners instead. In case an MRI is performed as part of routine clinical care within 48 h after CT imaging, the acquired FLAIR and DWI images will be used instead of performing an additional study MRI.

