### Statistical analysis

#### Ischemia detection

##### Sample size

Over 30,000 people suffer from an ischemic stroke in the Netherlands each year.^31^ About 30% of them will have an intracranial large artery occlusion, and 70% will have a minor stroke or TIA. As a result, 500 of the 720 subjects are possible candidates for small volume infarct detection. Assuming that at least half of the 500 patients will give informed consent for the extra follow-up MRI and do not have contra-indications for undergoing MRI, we should have 250 potential patients for the part of the study that concerns small volume stroke detection. Based on the historical cohort (Dutch Acute Stroke Study: 2009–2013, METC number 08–373), we expect to improve the sensitivity of CTP for small volume stroke detection from 0.45 to at least 0.75, which approaches the sensitivity of MRI (0.88–1.00).^32^ With a minimal acceptable lower 95% confidence level of 0.6 for the increased sensitivity, we will need about 107 MRI subjects.^33^ We expect that about 60% of patients with suspected stroke, and no large artery occlusion on admission will have an infarct on follow-up imaging.^34^ This means that we need to include at least 178 patients for the MRI part of this study.

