### Diagnostic value

The diagnostic properties to detect cerebral ischemia of both the standard CTP and the high-resolution CTP images will be compared to the reference standard (DWI). The DWI images will be evaluated by an experienced neuroradiologist. Sensitivity, specificity, positive predictive value, and negative predictive value with 95% confidence intervals will be calculated. We hypothesize that the high-resolution CTP will have superior sensitivity compared to the standard CTP for the detection of ischemia. The diagnostic values will be compared between the CTP protocols with the McNemar test and with receiver-operating characteristic (ROC) curves. A p-value lower than 0.05 will be considered significant.

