### Ethical considerations

Written informed consent will be acquired from patient or legal representative. The ability of the patient to give informed consent will be evaluated in order to determine whether the patient or the legal representative should be asked for written informed consent. Patients who are incapable of giving informed consent will not be asked to undergo MRI. In case the patient dies before informed consent can be acquired, the patient will be included without obtaining informed consent from his/her legal representative as it is undesirable to burden the legal representative with this request. The ENCLOSE study has been approved by the medical ethics committee of the University Medical Center Utrecht.

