## Discussion

CTP has good sensitivity (80%) and specificity (95%) for brain infarct detection.^10^,^11^ However, accurate detection of small volume infarcts is still difficult with CTP because of noise and limited spatial resolution.^38^ In addition, evaluation of the posterior fossa is often hampered by streak artefacts.^39^ In case no stroke is visualized with CT, an MRI is sometimes indicated to ascertain the diagnosis. By improving the detection of small volume stroke by CTP, additional MRI may become unnecessary in the diagnostic pathway, and early detection of these small ischemic strokes may influence acute treatment decisions.

Cardiac CTA may be a fast and noninvasive method for depicting cardiac thrombus in the acute stroke phase. It has some advantages over (delayed) echocardiographic imaging and may facilitate in starting anticoagulant treatment in time. Adding cardiac CTA to the standard stroke imaging protocol will cost an additional 2 s, and the additional radiation exposure will be marginal.

Prediction of recurrences has been subject of multiple studies.^25^ However, developed clinical models for long-term prediction have limited discriminative ability with c-statistics not greater than 0.7.^25^ Addition of imaging predictors to clinical models may improve their predictive value.

For this study, we will not exclude particular subgroups of patients with AIS for reasons of clinical applicability and generalizability. We select on acquisition timing as CT findings such as ischemia may differ between patients who present in an early time window when compared with patients who present in a late time window. Different kinds of CT scanners will be used as multiple centers are involved in this study. Although this can lead to heterogeneity of imaging acquisitions, it enables generalization of the results to other stroke centers.

In conclusion, the ENCLOSE study aims to increase the diagnostic accuracy of CTP for detection of small volume infarcts and diagnostic yield of CTA for cardioembolic sources. Besides, the study aims to improve prognostic models for predicting recurrent ischemic stroke. CT-derived predictors, including predictors derived from early cardiac CTA, will be used to improve prognostication of recurrent ischemic stroke.

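### Routine-care MRI can make the DWI reference depend on the standard CT result, so the sensitivities in patients with DWI, and their paired difference, can be biased

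*Protocol article*

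**What the plan says.** Under Study design and Inclusion and exclusion criteria, the protocol article selects patients for the MRI part by clinical diagnosis, CTA finding (no occlusion or a distal one) and absence of MRI contraindications. The CTP result is not a criterion.

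The Sample size section on ischemia detection starts from about 500 candidates: "Assuming that at least half of the 500 patients will give informed consent for the extra follow-up MRI" and are free of contraindications, it expects 250. It also states that "we expect to improve the sensitivity of CTP for small volume stroke detection from 0.45 to at least 0.75".

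The MR imaging section opens a second route to the reference. "In case an MRI is performed as part of routine clinical care within 48 h after CT imaging", its FLAIR and DWI images take the place of a study scan. On when such scans occur, the Discussion says: "In case no stroke is visualized with CT, an MRI is sometimes indicated to ascertain the diagnosis". Ethical considerations adds: "Patients who are incapable of giving informed consent will not be asked to undergo MRI". Such patients can still enter the cohort through a legal representative.

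The Diagnostic value section compares both CTP readings with DWI, using sensitivity, specificity, predictive values, a McNemar test and ROC curves. It hypothesizes higher sensitivity for the high-resolution reading. These measures need a DWI result, so only patients with DWI contribute.

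**The concern.** For a candidate who declines the study MRI, or cannot be asked, routine care is the only way to a DWI result, and the MR imaging section does not exclude such scans. If clinicians order MRI more often after a negative CT, patients negative on standard CTP are over-represented among those with DWI. Patients positive on thin-slice CTP only all belong to that group, so they gain weight relative to patients positive on both.

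The comparison is paired, but pairing controls for differences between patients only within the verified set. It does not undo selection into that set by one of the two tests being compared. At stake are the superiority claim and the absolute sensitivities. If CT-negatives are over-verified, the error in the difference favours the study hypothesis. Non-verification of patients unable to consent adds selection that is probably related to severity.

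**Working it through.** **The plan's own figures.** 720 × 0.70 = 504, stated as 500. 500 × 0.5 = 250 with MRI. 250 × 0.60 = 150 expected DWI-positives. The 107 DWI-positives needed are reproduced by an exact binomial test of 0.60 against 0.75 at one-sided 0.05 and power 0.95; the article states neither value. 107 / 0.60 = 178.3, stated as 178. Numbers are therefore adequate, and the question is who is verified.

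**Bias model.** Sensitivities of 0.45 and 0.75 are from the Sample size section. Assumed: every standard-positive infarct is also thin-slice positive, and verification depends only on the standard CTP result. The DWI-positive cells are then both positive 0.45, thin-slice only 0.30, neither 0.25. Let v+ and v− be the probability of DWI in standard-positive and standard-negative patients. The document gives neither, so they are assumed over a range.

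- Total T = 0.45·v+ + 0.30·v− + 0.25·v−
- Standard sensitivity = 0.45·v+ / T
- Thin-slice sensitivity = (0.45·v+ + 0.30·v−) / T
- Difference = 0.30·v− / T

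| v− / v+ | Weighted cells | T | Standard | Thin-slice | Difference |
|---|---|---|---|---|---|
| 0.50 / 0.50 | 0.225, 0.150, 0.125 | 0.500 | 0.45 | 0.75 | 0.30 |
| 0.55 / 0.45 | 0.2025, 0.165, 0.1375 | 0.505 | 0.40 | 0.73 | 0.33 |
| 0.60 / 0.40 | 0.18, 0.18, 0.15 | 0.51 | 0.35 | 0.71 | 0.35 |
| 0.40 / 0.60 | 0.27, 0.12, 0.10 | 0.49 | 0.55 | 0.80 | 0.245 |

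The first row shows that verifying half the candidates costs precision but causes no bias.

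**Two routes mixed.** The rows above apply the dependence to all MRIs. Suppose instead that 75% of MRIs come from the study route, unrelated to CTP, and 25% from routine care with a v−/v+ ratio of 3. Take prevalence 0.60 (Sample size section), specificity 0.95 (Background, for CTP in general; assumed for both readings here) and 5% of DWI-positives seen on standard CTP only (assumed).

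- Standard-positive share: 0.60 × 0.45 + 0.40 × 0.05 = 0.29
- Routine route: v+ = 0.125 / (0.29 + 3 × 0.71) = 0.052, v− = 0.155
- Adding 0.375 from the study route to each gives 0.427 and 0.530, a net ratio of 1.24
- Weighted cells (both 0.40, standard only 0.05, thin-slice only 0.35 × 1.242, neither 0.20 × 1.242) total 1.133
- Standard 0.45 / 1.133 = 0.397; thin-slice 0.835 / 1.133 = 0.737; difference 0.34

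With a routine-care ratio of 1.5 the difference is 0.32. With a 50/50 split of routes and ratios of 1.5 to 3, it is about 0.34 to 0.38.

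**No true difference.** Let both sensitivities be 0.45 with 10% discordant each way, 300 DWI-positive candidates, 50% verified overall and a net ratio of 2. The discordant counts are about 17.5 and 8.8 among 136 verified. The false difference is 8.8 / 136 = 0.065, with expected McNemar z = (17.5 − 8.8) / √26.3, about 1.7.

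**Specificity.** At a net ratio of 1.5, standard specificity reads (0.95 × 1.5) / (0.95 × 1.5 + 0.05) = 0.966 instead of 0.95.

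**Check of the correction.** Dividing the 0.60/0.40 cells by their verification probabilities gives 0.18/0.40 = 0.45, 0.18/0.60 = 0.30 and 0.15/0.60 = 0.25, which are the true cells.

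**The case against.** The main route to DWI does not look at CTP. Selection on CTA defines the target population and is not partial verification. A routine MRI in a patient who would have had the study MRI changes the source of the scan, not who is verified. The Discussion sentence says only sometimes, speaks of CT rather than the 5-mm CTP reading, gives no rate and describes practice in general. The clinicians' impression of the CT and the study observers' CTP reading may also differ, which would weaken the link. All of this stands. It limits the bias to patients verified through routine care alone, or to consent that follows the CT result.

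Three stronger readings are tempting, and the document supports none of them. A reader might infer that the estimates are biased; the text shows a route to bias, not its size. A reader might infer that only half of the eligible patients get DWI; the text gives a planning minimum that also absorbs contraindications, and contraindicated patients are not eligible for the MRI part. A reader might infer that the difference is inflated; with the opposite dependence it shrinks.

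It can also be said that candidates without DWI may be handled in the full protocol or analysis plan. That is so, and silence in the article is not the point here. The point is that the article's own rules interact to open this route, and a better analysis can be named.

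**Conclusion.** The concern holds as a possibility, not as a demonstrated bias. Verification can depend on the standard CT result through routine-care MRI, and on severity through capacity to consent. The verified-only sensitivities and their paired difference can then be off in either direction. Under the assumed verification rates, a true difference of 0.30 reads between about 0.25 and 0.35. If a quarter of MRIs come through routine care at ratios of 1.5 to 3, the shift is 2 to 4 points. It is zero if verification does not depend on CTP.

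Within this range the 0.60 lower limit is not threatened. At 0.60/0.40, a thin-slice sensitivity of 0.706 in 107 DWI-positives has an approximate lower limit of 0.706 − 1.96 × √(0.706 × 0.294 / 107) = 0.62. The standard sensitivity moves most, and with it the difference.

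These figures rest on the planned sensitivities and on assumed verification rates and discordance. The effect of not offering MRI to patients unable to consent was not quantified; the article gives no number for them.

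**What to change.** In Diagnostic value, add three things:

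1. Record for each DWI whether it came from a study or a routine-care MRI, and why it was done.
2. Report the accuracy results by MRI source as well as overall.
3. Beside the verified-only result, give as a sensitivity analysis a Begg-Greenes or inverse-probability-of-verification estimate of both sensitivities, both specificities and the paired difference. Take it over all MRI-part candidates, based on the standard CTP result, NIHSS, TIA versus stroke, capacity to consent and centre, with bootstrap intervals.

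The CT protocol is planned for all patients and NIHSS is baseline data, so this needs no new acquisition. It does need the standard CTP reading in unverified candidates. It assumes that verification depends only on recorded variables, which cannot be tested, and it widens the intervals slightly. If hardly any patients unable to consent have DWI, weighting cannot reach that group, and the report should then limit its conclusion to patients able to consent.

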#### Recurrence and clinical outcome

As part of routine care, patients will be contacted for follow-up evaluation at 90 days in the outpatient clinic or by telephone by stroke nurses, who are trained and certified to evaluate the modified Rankin scale (mRS). The 90-day clinical outcome of the patient will be evaluated with the mRS. A Dutch-structured questionnaire, which was based on previous studies, will be used to assess the mRS by telephone.^29^,^30^ In addition, patients will be asked for a second follow-up evaluation by telephone after two years. At two years, the patients will be asked whether a recurrent stroke has occurred and, if applicable, when and where the patient was treated for the recurrence. A discharge summary on the recurrent event will be requested from the hospital or general practitioner.

### Data entry and monitoring

Clinical data and imaging findings are registered with electronic case report forms in an online secured database (OpenClinica, LLC, Waltham, USA). Patient names and identification numbers will be replaced by a study code. To assess the quality and validity of the research data, independent and qualified monitors will be appointed to monitor the study in the participating centers.

### Statistical analysis

#### Ischemia detection

##### Sample size

Over 30,000 people suffer from an ischemic stroke in the Netherlands each year.^31^ About 30% of them will have an intracranial large artery occlusion, and 70% will have a minor stroke or TIA. As a result, 500 of the 720 subjects are possible candidates for small volume infarct detection. Assuming that at least half of the 500 patients will give informed consent for the extra follow-up MRI and do not have contra-indications for undergoing MRI, we should have 250 potential patients for the part of the study that concerns small volume stroke detection. Based on the historical cohort (Dutch Acute Stroke Study: 2009–2013, METC number 08–373), we expect to improve the sensitivity of CTP for small volume stroke detection from 0.45 to at least 0.75, which approaches the sensitivity of MRI (0.88–1.00).^32^ With a minimal acceptable lower 95% confidence level of 0.6 for the increased sensitivity, we will need about 107 MRI subjects.^33^ We expect that about 60% of patients with suspected stroke, and no large artery occlusion on admission will have an infarct on follow-up imaging.^34^ This means that we need to include at least 178 patients for the MRI part of this study.

### Diagnostic value

The diagnostic properties to detect cerebral ischemia of both the standard CTP and the high-resolution CTP images will be compared to the reference standard (DWI). The DWI images will be evaluated by an experienced neuroradiologist. Sensitivity, specificity, positive predictive value, and negative predictive value with 95% confidence intervals will be calculated. We hypothesize that the high-resolution CTP will have superior sensitivity compared to the standard CTP for the detection of ischemia. The diagnostic values will be compared between the CTP protocols with the McNemar test and with receiver-operating characteristic (ROC) curves. A p-value lower than 0.05 will be considered significant.

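### As worded, the McNemar comparison of standard and high-resolution CTP covers PPV and NPV, for which it is not a valid test (minor; the sensitivity hypothesis is unaffected)

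*Protocol article*

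**What the plan says.** The Diagnostic value section of the protocol article compares standard and high-resolution CTP, each judged against DWI in the same patients. It first names the measures: "Sensitivity, specificity, positive predictive value, and negative predictive value with 95% confidence intervals will be calculated". It then gives one hypothesis: "We hypothesize that the high-resolution CTP will have superior sensitivity compared to the standard CTP for the detection of ischemia". Next comes the comparison rule: "The diagnostic values will be compared between the CTP protocols with the McNemar test and with receiver-operating characteristic (ROC) curves". The significance threshold follows directly: "A p-value lower than 0.05 will be considered significant".

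No other method is named for the predictive values, and McNemar is not restricted to any of the four measures.

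On the CTP reading itself, the Analysis section under CT imaging says: "The obtained perfusion maps will be evaluated for the presence and location of a focal perfusion deficit". It mentions neither a graded score nor a continuous measure for this reading, and it excludes neither.

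**The concern.** The four listed measures are the natural antecedent of the comparison sentence, so the rule as written sends PPV and NPV to McNemar. McNemar needs each patient to contribute one pair of results to one 2x2 table. Sensitivity and specificity meet that need, because DWI fixes the group of patients and both protocols are read in all of them. Predictive values do not: the patients who count towards PPV are those positive on that protocol, and the two protocols pick out different, overlapping sets.

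At stake is any p-value reported for a difference in PPV or NPV. The Discussion suggests that better CTP may make additional MRI unnecessary. Support for that would rest partly on NPV, so the comparison is not purely decorative, although it is secondary to sensitivity.

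**Working it through.** **Inputs.** From Sample size under Ischemia detection: sensitivities 0.45 and 0.75, lower limit 0.60, 107 MRI subjects with infarct, infarct prevalence 60%, 178 patients in total. From Background: CTP specificity 0.95 for infarct detection in general. The article gives no specificity for either protocol in small volume stroke, so using 0.95 for both is an assumption.

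**1. The plan's own figures.** The article says: "With a minimal acceptable lower 95% confidence level of 0.6 for the increased sensitivity, we will need about 107 MRI subjects". Take the smallest n for which an exact one-sided 5% binomial test of 0.60 has at least 95% power at 0.75. This gives n = 107 (power 0.955). Then 107 / 0.60 = 178.3, against 178 stated. Both figures reproduce. They leave 178 − 107 = 71 DWI-negative patients.

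**2. Denominators of the predictive values.**

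- False positives, either protocol: 71 × 0.05 = 3.55. True negatives: 71 − 3.55 = 67.45.
- Standard CTP: true positives 107 × 0.45 = 48.15. Test-positives 48.15 + 3.55 = 51.7; PPV = 48.15 / 51.7 = 0.93. Test-negatives 178 − 51.7 = 126.3; NPV = 67.45 / 126.3 = 0.53.
- High-resolution CTP: true positives 107 × 0.75 = 80.25. Test-positives 80.25 + 3.55 = 83.8; PPV = 80.25 / 83.8 = 0.96. Test-negatives 178 − 83.8 = 94.2; NPV = 67.45 / 94.2 = 0.72.

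The assumed specificity matters little. For any common value, the test-positive counts differ by 107 × (0.75 − 0.45) = 32.1. At specificity 0.80, with 71 × 0.20 = 14.2 false positives, they are 62.35 and 94.45. At specificity 1.00 they are 48.15 and 80.25.

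**3. Can any McNemar table answer the PPV question?** There are three candidates.

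- *Patients positive on both protocols.* Each positive call is right or wrong according to the same DWI result, so no discordant pairs can occur and there is nothing to test.
- *All patients, test positivity.* This asks whether the two protocols call positives equally often, which is not PPV.
- *All patients, correctness.* This compares overall accuracy, which is not PPV.

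The last two were checked by simulation with PPV equal by construction: prevalence 0.60, sensitivities 0.45 and 0.75, false-positive rates 0.045 and 0.075. PPV is then 0.27 / (0.27 + 0.018) = 0.9375 for one protocol and 0.45 / (0.45 + 0.03) = 0.9375 for the other. With 178 patients, readings independent given DWI status, exact McNemar at 0.05 and 4,000 runs, the test on positivity rejected in 99% of runs and the test on correctness in 96%. Neither can serve as a test of PPV.

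**4. The stated hypothesis.** For McNemar in the 107 DWI-positive patients, let b be the proportion positive only on standard CTP and b + 0.30 the proportion positive only on high-resolution CTP. Put ψ = 2b + 0.30. Power at two-sided 0.05 is Φ[(0.30√107 − 1.96√ψ) / √(ψ − 0.09)]. For b from 0 to 0.1375 it runs from above 0.999 down to 0.990. That range includes readings independent given infarct, where b = 0.45 × 0.25 = 0.1125. The test is valid and well powered.

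**5. ROC.** If the reading is only present/absent, each protocol gives one operating point, and the area is (sensitivity + specificity) / 2: (0.45 + 0.95) / 2 = 0.70 and (0.75 + 0.95) / 2 = 0.85. These areas restate step 2's inputs and add no information.

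**The case against.** The strongest reply is that the comparison sentence is loose rather than wrong. It does not say that McNemar will be run on each measure, and it has a standard valid reading: sensitivity in DWI-positive and specificity in DWI-negative patients. The within-protocol confidence intervals promised for all four measures are sound whatever test is used. The single hypothesis and the sample size concern sensitivity alone. The simulated rejection rates also depend on how McNemar would be set up, which the article does not say.

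Most of this stands and limits the point to a minor one. It does not remove it: the sentence follows a list that includes PPV and NPV, names no other test for them, and is followed by a significance threshold. The simulation shows only that the available McNemar tables do not test PPV. It does not predict a particular false result in this study.

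A reader might go further in three ways that the article does not support.

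- *That the ROC comparison is invalid.* A binary reading gives a one-point curve, which is uninformative rather than invalid. Nothing limits the ROC input to the present/absent call, and the reading scale may be set out in the full protocol, which is not shown.
- *That a lower calling threshold could pass unnoticed as a better test.* Specificity with its interval is to be reported beside sensitivity, so such a trade would be visible. The article also does not say that the processed thin-slice maps are noisier.
- *That the sensitivity conclusion or the 107 and 178 figures are in doubt.* Steps 1 and 4 of the working show that they are not.

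**Conclusion.** The point holds for PPV and NPV. As worded, the article assigns them a test that cannot compare them, because the two protocols' denominators are different sets of patients: about 52 against 84 test-positives and 126 against 94 test-negatives among 178. Those counts rest on the article's planning sensitivities and prevalence and on an assumed common specificity of 0.95. The structural objection needs none of them. The consequence is confined to p-values for the secondary predictive-value comparisons, so the error is minor. The ROC question is a clarification only.

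**What to change.** Reword the comparison sentence in Diagnostic value as follows.

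- McNemar for sensitivity in DWI-positive patients (the stated hypothesis) and, separately, for specificity in DWI-negative patients.
- For PPV and NPV, either a paired predictive-value method (generalised or weighted score test, or a bootstrap that resamples patients) or estimates with 95% confidence intervals and no test.
- State what graded or quantitative CTP measure the ROC curves are built on. If the reading is only present/absent, drop the ROC comparison. Adding a reader confidence score is an option, not a requirement; it would have to be recorded at the time of reading.

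The cost is analysis wording. The PPV and NPV correction needs no further patients, imaging or data, and the sample size stays as it is.
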